### Outcome Measures

#### Primary Outcome

The primary outcome will be 70% fT > MIC, which is the target rate of 70% of patients having a free antimicrobial drug concentration exceeding the MIC during 70% of the dosing interval. 70% fT > MIC is appropriate to evaluate therapeutic efficacy of time dependent antibiotics in neonates (Craig, 1995; Wu et al., 2020). Based on PPK model of latamoxef, 70% fT > MIC will be calculated after testing plasma drug concentration at the initial stage of treatment (Table 3).

#### Secondary Outcomes

This trial has five secondary outcomes:1) Rate of latamoxef treatment failure: the symptoms and laboratory indicators of infection persist or worsen after latamoxef treatment. Neonatologists have to increase of the dose of latamoxef, or add other antibiotics to the treatment with latamoxef, or stop latamoxef treatment and switch to other antibiotics.2) Duration of antibiotic therapy: the length of antibiotic therapy for EONS;3) Changes of white blood cell count (WBC), CRP and PCT: comparison of the changes of WBC, CRP and PCT at baseline, initial stage of treatment (18–72 h) and before the end of treatment (Table 3);4) Blood culture results during administration: comparison of blood culture results at baseline, initial stage of treatment (18–72 h) and before the end of treatment (Table 3);5) Incidence of adverse events (AE)s: monitoring and recording AEs during latamoxef therapy (Table 3).

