## Abstract

Early-onset neonatal sepsis (EONS), a bacterial infection that occurs within 72 h after birth, is associated with high likelihood of neonatal mortality. Latamoxef, a semi-synthetic oxacephem antibiotic developed in 1980s, has been brought back into empirical EONS treatment in recent years. In the preliminary work, we established a population pharmacokinetics (PPK) model for latamoxef in Chinese neonates. Moreover, in order to better guide clinical treatment, we conducted dose simulation and found that ascending administration frequency could improve the target rate of 70% of patients having a free antimicrobial drug concentration exceeding the MIC during 70% of the dosing interval (70% fT > MIC). Accordingly, this study is aimed to compare the 70% fT > MIC, efficacy and safety between conventional regimen and PPK model regimen for rational use of latamoxef in EONS treatment. A single-blind, multicenter randomized controlled trial (RCT) for latamoxef will be conducted in Chinese EONS patients. Neonates (≤3 days of age, expected number = 114) admitted to the hospital with the diagnosis of EONS and fulfilling inclusion and exclusion criteria will be randomized (ratio of 1:1) to either a conventional regimen (30 mg/kg q12h) or model regimen (20 mg/kg q8h) latamoxef treatment group for at least 3 days. Primary outcome measure will be 70% fT > MIC and secondary outcome indicators will be the latamoxef treatment failure, duration of antibiotic therapy, changes of white blood cell count (WBC), C-reactive protein (CRP) and procalcitonin (PCT), blood culture results during administration and incidence of adverse event (AE)s. Assessments will be made at baseline, initial stage of latamoxef treatment (18–72 h) and before the end of latamoxef treatment. Ethical approval of our clinical trial has been granted by the ethics committee of the Beijing Children’s Hospital (ID: 2020-13-1). Written informed consent will be obtained from the parents of the participants. This trial is registered in the Chinese Clinical Trial Registry (ChiCTR 2000040064).It is hoped that our study will provide a clinical basis for the rational clinical use of latamoxef in EONS treatment.

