### Diagnostic Criteria of Early-Onset Neonatal Sepsis

The diagnostic criteria of EONS will refer to expert Consensus on the Diagnosis and Management of Neonatal sepsis (version 2019) (The Subspecialty Group of Neonatology, 2019).1) The suspected diagnosis of postnatal age in days (PNA) ≤3 contains any of the following: abnormal clinical manifestations, the mother has chorioamnionitis and premature rupture of membranes (PROM) ≥18 h. Sepsis can be ruled out if there are no abnormal clinical manifestations, including negative blood culture, and less than two consecutive non-specific blood tests (white blood cell count, immature neutrophil count, platelet count, C-reactive protein (CRP) and procalcitonin (PCT), etc.) at 24 h intervals.2) The patient has been clinically diagnosed with clinical abnormalities (Table 2) and met any of the following conditions at the same time: the blood non-specific tests ≥2 positive, the cerebrospinal fluid (CSF) test suppurative meningitis change, the pathogenic DNA detected in the blood.3) When the patient has clinical manifestations (Table 2), blood culture or CSF (or other sterile cavity fluid) culture positive, and the diagnosis confirmed.

**TABLE 2 T2:** Clinical manifestations of neonatal sepsis.

System	Clinical manifestations
Whole body	Fever, hypothermia, poor response, poor feeding, edema, low apgar score
Digestive system	Jaundice, abdominal distension, vomiting or gastric retention, diarrhea and hepatosplenomegaly
Respiratory system	Dyspnea, apnea, cyanosisetc.
Circulatory system	Pale face, cold limbs, bradycardia, tachycardia, marbled skin, hypotension or capillary filling time >3 s
Urinary system	Oliguria and renal failure
Blood system	Bleeding and purpura

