### Randomization and Blinding

To minimize selective bias, Beijing Six Yuan Space Information Technology Co., Ltd (Six Yuan) has been entrusted to conduct a stratified blocked randomization by using a computer random number generator in the system of Six Yuan. Participants will be randomly divided into the conventional treatment group and the model treatment group with a ratio of 1:1. The randomized code of the trial, derived from the random system of Six Yuan, will be the unique identification code of participants. After assignment of the randomization code, researchers are un-blinded to the treatment regimen of latamoxef. Considering that the drug concentration detection and data analysis will significantly affect the conclusion of this trial, all the research assistants in charge of drug concentration detection and statisticians will be blinded to treatment assignment until the trial is completed.

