### Intervention

After inclusion in the study, participants will be randomized into a conventional treatment group and a model treatment group. They will receive the following interventions at least 3 days. Conventional treatment group: latamoxef, 30 mg/kg q12h; model treatment group: latamoxef, 20 mg/kg, q8h. As steady-state plasma concentration of latamoxef will be reached after 18 h of dosing, the opportunistic blood sampling method will be used to collect samples for testing plasma drug concentration at initial stage of the treatment (18–72 h) (Table 3).

**TABLE 3 T3:** Study schedule of latamoxef RCT in EONS treatment.

Items	Study phases (The beginning of latamoxef treatment is set as 0 h)		
	Baseline (−3–−1 day)	Initial stage of treatment (18–72 h)	Before the end of latamoxef treatment
Informed consent form (ICF)	X		
Demographic information	X		
Medical history	X		
Diagnosis and determination of the treatment regimen	X		
Inclusion/exclusion criteria	X		
Get the random number	X		
Comorbid drug use	X	X	X
Weight	X	X	X
Vital signs^a^ and physical examination	X	X	X
Blood routine^b^	X	X	X
Blood culture	X	X	X
CRP and PCT	X	X	X
Liver and kidney function^c^ ^d^	X	X	X
Cerebrospinal fluid (CSF) examination (optional)^e^	X	X	X
Dose, frequency and time point of latamoxef administration		X	X
Detection of plasma latamoxef concentration		Random sampling point	
Sampling time of plasma samples		X	
Efficacy assessment			X
Adverse event assessment		X	X
Case report form (CRF)	X	X	X

a Vital signs include the temperature, blood pressure and oxygen saturation (SaO_2_).

b Blood routine tests include red blood cells, hemoglobin, white blood cells, and platelets.

c Liver function tests include alanine and aspartate aminotransferases, alkaline phosphatase level, total bilirubin, and gamma-glutamyl transferase.

d Kidney function tests include creatinine and blood urea nitrogen.

e CSF examination include CSF routine (characters, cells and Pandy’s test) and culture. This examination can be used when neonatologists suspect a patient has a neurological infection.

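### Treatment failure and antibiotic duration depend partly on decisions by clinicians who know the regimen, so a difference between arms can partly reflect knowledge of the arm

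*Protocol article*

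**What the plan says.** All references are to the protocol article.

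- **Label.** The Abstract says: "A single-blind, multicenter randomized controlled trial (RCT) for latamoxef will be conducted in Chinese EONS patients".
- **Who is blinded.** Under Randomization and Blinding: "After assignment of the randomization code, researchers are un-blinded to the treatment regimen of latamoxef". The same section says that "all the research assistants in charge of drug concentration detection and statisticians will be blinded to treatment assignment until the trial is completed", and gives its reason as "Considering that the drug concentration detection and data analysis will significantly affect the conclusion of this trial". Clinical outcome assessment is not mentioned.
- **Regimens.** Under Intervention: "Conventional treatment group: latamoxef, 30 mg/kg q12h; model treatment group: latamoxef, 20 mg/kg, q8h". No masking of the schedule is described.
- **Treatment failure.** Under Secondary Outcomes there are two parts. The condition is that "the symptoms and laboratory indicators of infection persist or worsen after latamoxef treatment". The decision is "Neonatologists have to increase of the dose of latamoxef, or add other antibiotics to the treatment with latamoxef, or stop latamoxef treatment" and change to other antibiotics.
- **Other secondary outcomes.** These are duration of antibiotic therapy; changes in WBC, CRP and PCT; blood culture results; and adverse events. Table 3 schedules blood routine, CRP, PCT and blood culture at baseline, at 18–72 h and before the end of treatment.

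**The concern.** A failure event needs a clinician to act. That clinician can see whether the infant is dosed every 8 or every 12 hours, in a trial whose premise is that the more frequent schedule reaches the PK/PD target more often (80.1% against 60.2% in Sample Size Estimates). Two infants with the same borderline course could be handled differently because of the arm. The statisticians would then analyse, blinded, an event that was already shaped by un-blinded judgement; blinding the analysis cannot undo that. The length of antibiotic therapy is set by similar decisions.

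At stake is how a difference in failure is read. If fewer failures are recorded on the model regimen, a reader may take this as clinical support for the PK/PD result when part of it comes from knowing the arm.

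**Working it through.** **Step 1. Who determines each outcome, and does that person know the arm?**

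| Outcome | What determines it | Exposure to knowledge of the arm |
|---|---|---|
| Primary: 70% fT > MIC | Measured concentration and the PPK model; assay staff and statisticians blinded | Low |
| Treatment failure | Symptoms and laboratory indicators, plus a clinician's change of therapy | Substantial |
| Duration of antibiotic therapy | Clinicians' decisions on therapy | Substantial |
| WBC, CRP, PCT, blood culture | Laboratory measurements at scheduled stages | Low |

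One link is inferred. The article says researchers are un-blinded and does not say that these include the treating neonatologists. The inference is strong, because someone at the bedside must order and give q8h or q12h, and Recruitment Strategies puts physicians of the neonatal units in charge of enrolment.

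**Step 2. How large could the effect be?** The documents give no failure rate, so there is no planned figure to reproduce. What follows is an illustration on assumed values.

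Let p be the true failure rate in both arms, f the fraction of all infants who are not true failures but are open to an extra change of therapy, and d the proportion of these changed on q12h only because the arm is known. Then:

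observed q12h failure = p + f × d; spurious difference = f × d.

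Take p = 0.15.

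- *Widest base, every non-failing infant (f = 0.85):* d = 0.05, 0.10, 0.15 gives 0.15 + 0.0425 = 19.3%, 0.15 + 0.085 = 23.5%, 0.15 + 0.1275 = 27.8%. The spurious difference is 4.3, 8.5 and 12.8 points.
- *Half that base (f = 0.425):* the difference halves, to 2.1, 4.3 and 6.4 points.

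The widest base is an upper bound for a given d. An infant whose signs and laboratory values have resolved does not meet the first part of the definition, whatever the clinician does.

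**Step 3. What would that do to the test?** Exact enumeration, 57 per arm, uncorrected chi-square test at two-sided 0.05, counting only results in favour of the model regimen:

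| Spurious difference (points) | Chance of p < 0.05 favouring the model regimen |
|---|---|
| 0 | 2.5% |
| 4.3 | 9% |
| 8.5 | 21% |
| 12.8 | 39% |

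With half the base (2.1, 4.3 and 6.4 points) the chances are 5%, 9% and 14%. With 64 per arm the widest-base figures are 9%, 22% and 42%. Over a wider set of assumptions (true failure 10% to 30%, excess 5 to 15 points, 57 per arm) a normal approximation gives about 8% to 56%.

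These figures show that a modest shift in decisions would matter at this sample size. They do not estimate the shift.

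**The case against.** The case on the other side is substantial, and much of it stands.

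- **A reader might infer that failure is the main clinical outcome.** The article only lists it first of five secondary outcomes and states no ranking. The sample size rests on the PK/PD outcome alone. This stands.
- **A reader might infer that the clinician's decision alone defines failure.** It does not: symptoms and laboratory indicators must also persist or worsen. This stands, and it shrinks the group in which bias can act. It does not remove the decision from the definition.
- **A reader might infer that the single-blind label hides the un-blinding.** It does not: Randomization and Blinding says openly who knows the regimen and who does not. What is missing there is only the consequence for the clinical outcomes.
- **A reader might infer that the blinding protects the primary outcome and nothing else.** WBC, CRP, PCT and blood culture are separate laboratory outcomes and offer a cross-check on a failure difference.
- **A reader might count signs in Table 2 that cannot resolve, such as a low Apgar score, as persistence.** Table 2 serves diagnosis, and the failure definition does not cite it.
- **The lack of a numerical threshold for persistence** is detail that an article commonly leaves to the full protocol, so it is not raised here.
- **The direction of bias is not proven.** Both arms receive 60 mg/kg per day (2 × 30 = 3 × 20), and the stated expectation concerns target attainment, not clinical failure. This stands, so a bias towards the model regimen is plausible but not shown.
- **Replacing failure with a programmed clinical rule would not cure it.** Bedside signs are still recorded un-blinded, the last assessment before a change could be baseline, and dosing records could un-blind the statisticians. For these reasons the definition is best kept and split.

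**Conclusion.** The point holds in a limited form. Treatment failure and antibiotic duration are, in effect, open-label outcomes: they depend in part on decisions by clinicians who can tell the arms apart, and blinding the assay staff and statisticians does not change that. The primary outcome and the laboratory secondary outcomes are much less exposed.

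The size of the bias is unknown. The illustrative 4 to 13 points rest on an assumed 15% failure rate, assumed extra changes in one arm only, and the widest possible base; they should not be quoted as an estimate. The conclusion also rests on the inference that treating neonatologists are among the un-blinded researchers.

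The documents do not support the stronger reading that the trial's efficacy result is invalid or that the un-blinding is concealed. What they support is that a difference in failure, taken alone, cannot carry an efficacy claim. This is worth correcting because the correction is cheap and uses scheduled data.

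**What to change.** Keep the definition under Secondary Outcomes and add component reporting by arm:

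1. **Laboratory and culture component.** Persistence or worsening, derived by the blinded statisticians with one prespecified rule from the post-baseline WBC, platelets, CRP, PCT and blood culture already scheduled in Table 3.
2. **Clinician component.** Any clinician-initiated change of therapy, with type, date and recorded reason, passed to the statisticians without dose or frequency so that they stay blinded.
3. **Interpretation.** Base any efficacy statement about failure on whether the first component agrees with the composite. If only the clinician component differs between arms, say so and do not present it as evidence of efficacy.
4. **Blinding statement.** Add to Randomization and Blinding that treatment failure and duration of antibiotic therapy are assessed open-label.

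None of this alters how infants are treated.

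Cost: one eCRF field for the reason for change, one programmed derivation and a few sentences of text; no extra visit, sample or assessor. Two limits remain. The laboratory component may miss failures seen only at the bedside, which the composite still captures. Laboratory values taken after a change partly reflect the new therapy, so the rule should say in advance which measurements count, and infants without a usable post-baseline value should be counted separately.

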### Study Data and Statistical Analysis Plan

The procedures and contents of data collection for this trial are detailed in Table 2. Demographic information, diagnosis, clinical data and laboratory data at baseline will be recorded on electronic case report form (eCRF) platform provided by Six Yuan (Table 2). In addition, clinical data, laboratory data and AEs at every planed time point after initiation of treatment will also be recorded in this eCRF platform (Table 2). According to the data collection methods and standards formulated by project director and researchers, all data of eCRF platform will be recorded in a true, detailed and careful manner to ensure the authenticity of the data.

Statisticians, independent of all the other processes, will conduct the statistical analyses by using SPSS version 15.0 for Windows (Chicago, IL, United States). The statisticians will calculate the mean, standard deviation, median, minimum, maximum, lower quartile (Q1), upper quartile (Q3) for quantitative data and describe numbers and percentages for qualitative data (Wang et al., 2020). Comparisons between two groups will be conducted as following: t-tests or Wilcoxon rank-sum for normal or nonnormal ability distributions for quantitative data; chi-square test or Fisher’s exact test for qualitative data (Wang et al., 2020). Analysis for missing data performed on the intention-to-treat principle. For all analysis, *p* value < 0.05 will be considered statistically significant.

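### WBC, CRP and PCT are compared at a 54 h wide visit and at an end-of-treatment visit whose timing follows response; the plain two-group tests ignore draw time

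*Protocol article*

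**What the plan says.** **Outcome.** The third item under Secondary Outcomes is a "comparison of the changes of WBC, CRP and PCT at baseline, initial stage of treatment (18–72 h) and before the end of treatment".

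**Schedule.** Table 3 (Intervention section) sets the clock with "The beginning of latamoxef treatment is set as 0 h". It gives blood routine, CRP and PCT a mark at baseline, at 18–72 h, and in a last column headed "Before the end of latamoxef treatment". No target hour is set inside the 18–72 h window, and the last column has no hour or day. The table lists sampling time only for the plasma samples.

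**Course length.** "They will receive the following interventions at least 3 days". No fixed length or maximum is given. Length of therapy is itself an outcome: "Duration of antibiotic therapy: the length of antibiotic therapy for EONS". The treatment-failure definition covers infants whose symptoms and laboratory indicators persist or worsen, and one of the listed responses is to "stop latamoxef treatment and switch to other antibiotics".

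**Blinding.** Under Randomization and Blinding, researchers know the regimen once the code is assigned. Those who measure drug concentrations and the statisticians do not.

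**Analysis.** For two-group comparisons the Study Data and Statistical Analysis Plan section names "t-tests or Wilcoxon rank-sum for normal or nonnormal ability distributions for quantitative data", with significance at p < 0.05.

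**The concern.** Inflammatory markers in treated infants can change quickly, so a value means little without its time. The stated tests compare values as if they were taken at the same time. At the two on-treatment visits this has different consequences.

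- **End of treatment.** The draw time is fixed after randomisation by how long the course lasts, and course length can respond to how the infant is doing. The arms are then compared at times that may themselves be an effect of the regimen. A difference in course length can appear as a marker difference, and a real difference in recovery can be absorbed into course length and vanish from the marker.
- **18–72 h.** Randomisation balances draw times on average unless something ties them to the arm. The spread of times then only adds noise.

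At stake is how one of five secondary outcomes is read. The primary outcome does not depend on it.

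**Working it through.** The protocol gives no figure for this outcome, so there is none to reproduce. The check uses the schedule, then an illustration under stated assumptions.

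**1. Do the two visits stay apart?**
The first window runs from 18 to 72 h, so its width is 72 − 18 = 54 h. The shortest planned course is 3 days = 72 h, which is the upper edge of that window. A draw taken before the end of a course of about 72 h therefore falls inside the first window. Longer courses need not overlap.

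**2. Precision at 18–72 h**
Assumptions not in the protocol: the marker halves every 24, 36 or 48 h; draw times are uniform over the window in both arms; the between-infant SD is 0.8 on the natural-log scale.

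- SD of draw time = 54/√12 = 15.6 h
- Added log SD = 15.6 × ln 2 / half-time
- Fold change from 18 to 72 h = 2^(54/half-time)
- Extra variance = (added SD)² / 0.8²
- Equivalent loss of infants = 1 − 1/(1 + extra variance)

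| Half-time | Fold change 18→72 h | Added log SD | Extra variance | Equivalent loss of infants |
|---|---|---|---|---|
| 24 h | 4.8 | 0.45 | 32% | 24% |
| 36 h | 2.8 | 0.30 | 14% | 12% |
| 48 h | 2.2 | 0.23 | 8% | 7% |

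If the SD is 1.2 instead, the extra variance falls to 0.45²/1.44 = 14% at a 24 h half-time and 0.225²/1.44 = 4% at 48 h.

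**3. False positives when the regimen has no effect on the marker at any given time**
Simulation: 57 per arm (Sample Size Estimates), two-sided t-test at 0.05, 4,000 runs per scenario, half-times and SD as in step 2. End-of-treatment draws are normal with SD 36 h and a floor of 72 h (assumed). Nominal mean courses are 168 h in both arms (same timing), 156 against 144 h (12 h shorter), and 168 against 144 h (24 h shorter).

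| Scenario | 24 h | 36 h | 48 h |
|---|---|---|---|
| 18–72 h, same draw times in both arms | 5.1% | 4.6% | 4.9% |
| 18–72 h, one arm drawn 6 h later on average | 17% | 11% | 9% |
| 18–72 h, one arm drawn 12 h later on average | 55% | 31% | 20% |
| End of treatment, same timing | 5.6% | 5.4% | 4.9% |
| End of treatment, one arm 12 h shorter | 28% | 21% | 16% |
| End of treatment, one arm 24 h shorter | 80% | 63% | 47% |

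Hand check of one cell (24 h half-time, 24 h shorter). Rate of decline = ln 2/24 = 0.0289 per h. Variance per infant = 0.8² + (0.0289 × 36)² = 0.64 + 1.08 = 1.72. Standard error = √(2 × 1.72/57) = 0.246. The simulated mean difference is 0.687, so z = 2.80 and the rejection rate is about Φ(2.80 − 1.96) = 80%, as simulated.

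**4. The opposite direction**
The simulation takes course length as unrelated to the infant's own marker. If instead courses ended when a marker reached some level, both arms would be measured near that level and faster recovery would show as a shorter course, not a lower marker. If failure ends latamoxef early, some last draws are taken while markers are poor. These mechanisms push in different directions, and the protocol does not say which dominates.

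**The case against.** The best defence is that a journal article condenses the protocol, and that models and handling of actual draw times belong in a fuller plan. That covers missing detail, but the article does state the windows and the tests, and those are what is questioned here.

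Several stronger readings are tempting, and the document does not support them:

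- *Both visits are biased.* Not at 18–72 h if draw times are similar by arm: the error rate stays at about 5%. Opportunistic sampling is stated for plasma drug concentration, not for these markers. A shift between arms is possible, since researchers are unblinded and the regimens are q8h and q12h, but nothing states it.
- *One draw serves both visits.* Table 3 gives the phases separate columns, each with its own mark. Overlap is possible only for courses ending near 72 h, and even then two draws could be taken.
- *The last visit pulls the arms together because infants stop when markers look good.* No marker-based stopping criterion is given, and the failure definition allows stops when markers are bad.
- *These are the only objective efficacy outcomes.* Blood culture results are also a secondary outcome, although the Discussion expects few positives.

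It is also fair to say that the sizes are assumed. Half-times, SD and draw-time distribution all come from outside the protocol, a single steady decline may suit WBC poorly, and the relevant SD for a change score is that of the change. The article nowhere says it will infer similar efficacy from these markers.

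**Conclusion.** The concern holds in limited form and is of minor weight.

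- **End-of-treatment comparison.** It is made at a post-randomisation time that can depend on response and is open to unblinded staff. Neither a difference nor its absence can be read as a marker effect unless course length is similar by arm, and the direction of any distortion is unknown. In the illustration, a 12–24 h difference in mean course gives 16–80% false positives across the assumed half-times. That staff set the end of the course is inferred from its open length and the failure definition; no sentence says so outright.
- **18–72 h comparison.** It mainly loses precision: about 8–32% more variance at a log SD of 0.8, and about 4–14% at 1.2. Bias needs draw times that differ by arm.
- **Overlap.** The visit windows can overlap for courses ending near 72 h. How many courses end there is not stated.

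**What to change.** Replace the plain two-group tests for this outcome with the following:

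1. Analyse CRP and PCT on the log scale, and WBC too if skewed, by ANCOVA or a repeated-measures model with baseline value, arm and actual hours since first dose. Add an arm-by-time term if the arms are allowed to diverge.
2. Report the arm difference at one pre-stated time within the 18–72 h window, for example 48 h, as the marker result.
3. Count a draw that falls in both windows once.
4. Label the end-of-treatment comparison descriptive and show it beside course length by arm. Adjusting for hours does not fully repair timing that depends on response.

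**Cost.** Analysis work, and an assumed smooth time trend. The clock time of each marker draw must be confirmed as recorded, because Table 3 lists sampling time only for plasma samples. No change to treatment, visits or sample size is needed. The change should be settled before the statisticians are unblinded.
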